### 6.7.3 Prohibited Medications

Prohibited from randomisation

| Class of prohibited medications                |                                                                    | Examples
(not comprehensive list)                                                                                                                                                                                                                                                                                           | Minimum washout periods prior to study medication dosing             |
|------------------------------------------------|--------------------------------------------------------------------|--------------------------------------------------------------------------------------------------------------------------------------------------------------------------------------------------------------------------------------------------------------------------------------------------------------------------------|----------------------------------------------------------------------|
| Anxiolytics, sedative hypnotics                | Benzo-diazepines                                                   | Alprazolam, clonazepam, diazepam, flurazepam, lorazepam, quazepam, triazolam, temazepam (see table above for allowed and intermittent use for insomnia)                                                                                                                                                                        | ≥7 days                                                              |
| Used for pain or may confound pain measurement | Barbiturates/
barbiturate combinations/
belladonna alkaloids | Amobarbital, butabarbital, metharbital, pentobarbital, phenobarbital, secobarbital, atropine sulfate, hyoscyamine sulfate, scopolamine hydrobromide, antrocol (atropine and Phenobarbital) butibel (belladonna and butabarbital), donnatal (atropine sulfate, hyoscyamine sulfate, scopolamine hydrobromide and Phenobarbital) | ≥7 days                                                              |
|                                                | Antiepileptics                                                     | Levetiracetam, carbamazepine, clonazepam, pregabalin, lamotrigine, phenytoin, topiramate and valproic acid                                                                                                                                                                                                                     | ≥7 days                                                              |
|                                                | Oral/IV/
per-rectum
corticosteroids                          | Dexamethasone, hydrocortisone, methylprednisolone, prednisolone, triamcinolone                                                                                                                                                                                                                                                 | ≥7 days                                                              |
| Medication used for control of nausea/vomiting | Anti-emetics                                                       | Corticosteroids and neuroleptic anti-emetics excluding metaclopramide. See above table for allowable                                                                                                                                                                                                                           | ≥7 days                                                              |
| Potential retinotoxins                         | Potential retinotoxins                                             | Hydroxychloroquine, deferoxamine, thioridazine, vigabatrin                                                                                                                                                                                                                                                                     | Participants who have ever take these are not eligible for the study |
| Others                                         | Monoamine oxidase inhibitors (MAOIs)                               | Phenelzine, tranylcypromine, moclobemide, socarboxazid                                                                                                                                                                                                                                                                         | MAOIs ≥21 days                                                       |

|  |                                                             |                                                                                                                                                             |                              |
|--|-------------------------------------------------------------|-------------------------------------------------------------------------------------------------------------------------------------------------------------|------------------------------|
|  | Other psychoactive drugs with psychoactive effects          | Amphetamines, cannabis, cocaine, dimethyltryptamine (DMT), dimethoxymethylamphetamine (DOM or "STP"), heroin, LSD, Ecstasy, PCP (phencyclidine), psilocybin | ≥14 days                     |
|  | Herbal psychoactive and miscellaneous supplement treatments | St John's Wort, α-lipoic acid, chromium picolinate, evening primrose oil, fatty acid supplements, myoinositol                                               | ≥14 days                     |
|  | Peripherally acting antiadrenergic                          | Guanethidine monosulfate                                                                                                                                    | ≥3 months                    |
|  |                                                             | Sympathetic blocks, acupuncture, botox, any other non-pharmacological treatment involving needle                                                            | ≥3 months                    |
|  | Electro-analgesia/ electrotherapy                           | Transcutaneous electrical nerve stimulation (TENS)                                                                                                          | Prohibited during the study. |

## 7 STUDY ASSESSMENTS

### 7.1 SAFETY ASSESSMENTS

- Medical history
- Pregnancy test
- Prior and concomitant medications
- Adverse events

### 7.2 STUDY ASSESSMENTS

(See Appendix 5 for additional detail)

Baseline (0 months): **Visit 1**

Informed consent

Screening

Eligibility confirmed

Randomisation to gabapentin or placebo

Treatment diary

Questionnaire

Week 1 Telephone interview

Week 2 Telephone interview (if dose escalation not finished)

Week 3 Telephone interview (if dose escalation not finished)

Week 4 Telephone interview (if dose escalation not finished)

Week 5 Telephone interview (if dose escalation not finished)

Week 6 (+/- 7 days) **Visit 2**

Short interview

Dispensing of drugs if necessary

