#### **6.3 DOSING REGIME**

Participants will start on 300mg gabapentin daily and will increase in 300 mg increments each week until they report a 50% pain reduction, or side effects (eg dizziness, somnolence, mood changes, appetite and poor concentration), up to a maximum dose of 2700 mgs. Patients will be advised regarding their dosing regime weekly by a member of the research team who will phone until optimum dose is reached. It will be recommended that the drug should be taken in three equally divided doses daily. Participants will be advised to remain on the maximum tolerated dose for up to 6 months. The same protocol will be used for the placebo. When the participant stops treatment then the dose will be tapered down over 7 - 10 days at the clinician's discretion.

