#### **6.4 DOSE CHANGES**

See above. If side effects prevent escalation of the dose one week then participants will be advised to try and increase the drug the following week.

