## 10 ADVERSE EVENTS

The Investigator is responsible for the detection and documentation of events meeting the criteria and definitions detailed below.

Participants will collect information about adverse events in their treatment diaries. However, they will be instructed to contact the clinical research team at any time after consenting to join the trial if they have an event that requires hospitalisation, or an event that results in persistent or significant disability or incapacity. The participants will be contacted weekly by a member of the research staff until they have reached their optimal dosage. Gabapentin is generally well tolerated in the management of other chronic pain conditions and SAEs are not anticipated. Any SAEs that occur after joining the trial will be reported in detail in the participant's medical notes and followed up until resolution of the event.

Full details of contraindications and side effects that have been reported following administration of the IMP can be found in the relevant Summary of Product Characteristics (SmPC).

Participants will be instructed to contact their Investigator at any time after consenting to join the trial if any symptoms develop. All adverse events (AE) that occur after joining the trial will be reported in detail in the Case Report Form (CRF) or AE form. In the case of an AE, the Investigator will ensure that the appropriate treatment is instigated by the appropriate medical personnel. Participants with AEs present at the last visit must be followed up until resolution of the event.

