### 10.2 DETECTING AEs AND SAEs

All AEs and SAEs will be recorded from the time a participant signs the consent form to take part in the study until end of treatment.

Participants will be asked to record the occurrence of AEs/SAEs in their treatment diaries during the study. They will not be asked to document the occurrence of any common ailments not associated with the drug eg colds and coughs. Open-ended and non-leading verbal questioning of the participant will be used to enquire about AE/SAE occurrence. Participants will also be asked if they have been admitted to hospital, had any accidents, used any new medicines or changed concomitant medication regimens. If there is any doubt as to whether a clinical observation is an AE, the event will be recorded. Participants will also be asked to record occurrence of any AEs in their daily treatment diaries. The participant's mood will be monitored by the research team using open ended questions during phone consultations and through the use of questionnaires at 3 and 6 months eg Hospital Anxiety and Depression Scale.

AEs and SAEs may also be identified by support departments e.g. laboratories.

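### Weekly staff questioning about adverse events and mood stops when titration stops, so how often a woman is asked depends on her response and tolerability and may differ between arms

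*Protocol*

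**What the plan says.** **Contact schedule.** Section 7.2 lists a telephone interview at week 1 without condition. From the next week it is conditional: "Week 2 Telephone interview (if dose escalation not finished". Weeks 3, 4 and 5 carry the same condition. A visit for every woman follows at week 6, with others at 3 and 6 months.

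**The same rule elsewhere.** Section 6.3 says that women are advised on dosing "weekly by a member of the research team who will phone until optimum dose is reached". Section 10, on adverse events, says: "The participants will be contacted weekly by a member of the research staff until they have reached their optimal dosage".

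**What ends escalation.** Under section 6.3 women "increase in 300 mg increments each week until they report a 50% pain reduction, or side effects", "up to a maximum dose of 2700 mgs". Section 6.4 adds: "If side effects prevent escalation of the dose one week then participants will be advised to try and increase the drug the following week". The placebo arm follows the same rules.

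**What the contacts are used for.** Section 10.2 states: "Open-ended and non-leading verbal questioning of the participant will be used to enquire about AE/SAE occurrence". It also says that mood will be "monitored by the research team using open ended questions during phone consultations", together with questionnaires at 3 and 6 months.

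**The concern.** The calls have two jobs. They deliver dosing advice, and they are one of the ways in which adverse events and mood changes come to light. Tying them to unfinished titration is natural for the first job. For the second, it makes the intensity of observation depend on pain response and tolerability, both of which treatment may change. Blinding and identical rules in the two arms do not prevent this, because one rule applied to different responses gives different numbers of calls.

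Mood is the clearest case. Section 6.3 names mood change among the side effects that can halt escalation, so the symptom being watched for can end the calls that watch for it. Between baseline and 3 months, these calls are the only mood monitoring that section 10.2 specifies.

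At stake are the descriptive adverse event and mood data from the titration weeks, and a contact schedule that could be carried into the main trial. Analysis cannot recover an event that nobody asked about.

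**Working it through.** The protocol gives no figure for the number of calls and no rate at which women finish escalation. The mechanism can be read from the text. Its size can only be illustrated.

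**Step 1: what can end the calls in weeks 2 to 5.** The start is 300 mg, the weekly step 300 mg and the maximum 2700 mg (6.3). The number of increments needed is (2700 − 300) / 300 = 8. With one step per week the maximum cannot be reached by week 5. Within the conditional calls listed in 7.2, the only reasons in 6.3 for finishing escalation are therefore pain reduction and side effects.

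**Step 2: range for one woman.** On the 7.2 schedule she has between 1 and 5 calls. If calls follow a full titration without deferred steps, the range is 1 to 8.

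**Step 3: expected calls.** Let q be the weekly probability of finishing escalation, assumed constant, and K the last week in which a call is possible. Week 1 is certain, and week k takes place if escalation has not finished earlier:

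E(calls) = Σ (1 − q)^(k−1), for k = 1 to K

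For K = 5:
- q = 0.25: 1 + 0.75 + 0.5625 + 0.4219 + 0.3164 = 3.05
- q = 0.10: 1 + 0.90 + 0.81 + 0.729 + 0.6561 = 4.10

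| q (assumed) | K = 5 (7.2 schedule) | K = 8 (full titration) |
|---|---|---|
| 0.10 | 4.10 | 5.70 |
| 0.20 | 3.36 | 4.16 |
| 0.25 | 3.05 | 3.60 |
| 0.30 | 2.77 | 3.14 |
| 0.40 | 2.31 | 2.46 |

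**Step 4: differences between arms for K = 5.**
- Gabapentin 0.25, placebo 0.10: 3.05 versus 4.10, about one call fewer on gabapentin.
- Gabapentin 0.40, placebo 0.10: 2.31 versus 4.10, about 1.8 fewer on gabapentin.
- Both 0.10: 4.10 versus 4.10, no difference.
- Gabapentin 0.10, placebo 0.20: 4.10 versus 3.36, about 0.7 more on gabapentin.

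**Step 5: sign.** Pain relief shortens escalation. Side effects shorten it if they end escalation (6.3) and lengthen it if the step is tried again the next week (6.4). The protocol does not say how often each happens, so the sign of any difference between arms is open.

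**Step 6: the call schedule itself.** Section 7.2 lists calls to week 5 and a visit at week 6. Sections 6.3 and 10 continue weekly contact until the optimum dose, and a woman who goes to 2700 mg needs eight weekly increments. The two descriptions do not agree for anyone still escalating after week 6.

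**The case against.** The strongest reply is that adverse events are also captured by routes that do not depend on titration. Every woman keeps a daily diary that includes adverse events, attends visits at week 6, 3 months and 6 months, completes HADS at 3 and 6 months, and is told to contact the investigator if symptoms develop. Section 10.2 does not confine verbal questioning to the calls. A side effect that stops escalation would normally be reported in the contact that acts on it. The primary endpoints concern recruitment, and medication-taking with questionnaire completion. Section 9.2 states no comparison of adverse events between arms, and it draws acceptability from focus groups, 6-month questionnaire items and diaries, not from the calls.

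Most of this stands, and it limits the point to events and mood changes that only a call in the titration weeks would bring out. It does not remove it. The diary is collected at 6 months, women are asked to leave out common ailments unrelated to the drug, and the protocol itself sets out to measure how well diaries are kept. The visit lists in 7.2 name no adverse event or mood enquiry, only a brief interview at week 6 and questionnaires later.

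Three stronger readings are tempting, and the document does not support them:
- **That the arms will differ.** This needs unequal finishing rates, and the protocol gives none.
- **That gabapentin harms will be under-detected** because women on placebo are questioned longer. Section 6.4 allows side effects to prolong contact, so the sign could be the reverse.
- **That staff contact covers only 5 of 26 weeks (19%).** This takes the 7.2 call list alone, against 6.3 and 10, and leaves out the fixed visits.

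**Conclusion.** The concern holds in a limited form. The protocol makes the frequency of staff questioning about adverse events and mood depend on pain response and tolerability, so it may differ between arms, in a direction that cannot be known in advance. On the 7.2 schedule a woman may have one to five calls. Under assumed weekly finishing probabilities of 25% and 10% the arms differ by about one call (3.1 versus 4.1), and under equal probabilities by none. These figures rest on invented values of q held constant over time, and show scale only.

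The consequence is confined to call-elicited reports during titration and to descriptive safety and mood data. It does not reach the feasibility conclusions. It still merits a change, because the contact rule is fixed in the protocol and the remedy is cheap. Separately, the duration of weekly contact is described inconsistently and must be reconciled.

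**What to change.** In section 7.2, remove the condition from the adverse event and mood questions, so that every woman is asked the same questions in weeks 1 to 5 whether or not escalation has finished. Align sections 10 and 10.2 with this. Dosing advice under 6.3 and 6.4 stays as it is; only the questioning is made unconditional.

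The cost is at most four short extra calls per woman (weeks 2 to 5) by existing staff, or at most 60 × 4 = 240 calls across the trial. In return, call-based ascertainment in those weeks is the same in both arms by design, and the gap in early mood monitoring closes for women who finish escalation early.

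Also reconcile 7.2, which lists calls only to week 5, with 6.3 and 10, which continue weekly contact until the optimum dose. Which schedule is intended is for the investigators to state. If calls run longer, common questioning should run to the same week for everyone. At eight weeks the upper limit becomes 8 − 1 = 7 extra calls per woman.

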### 3 months (+/- 7 days) **Visit 3**

Questionnaire  
Dispensing of drugs if necessary  
Brain fMRI (Edinburgh subset)

### 6 months(+/- 7 days) **Visit 4**

Questionnaire  
Unblinding  
Collection of treatment diary  
Collection of any unused study medications

3 - 6 months              Focus groups (subset)

The following measures will be completed by the subject in a daily treatment diary beginning on Day 1 of treatment.

- Time and dose of gabapentin taken
- Reason for any change in trial medication dose
- Concomitant medications taken
- Alternative therapies used
- Any visits to a healthcare professional
- Adverse events
- Weekly average Lickert pain score

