# 3 STUDY DESIGN

A two-arm parallel randomised controlled pilot trial. This will be a two centre pilot study with sites in NHS Lothian and NHS Grampian. We will recruit 60 patients over approximately nine months. After randomisation the participants will receive treatment for six months. Participants and the health care team will be unblinded at the end of their treatment.

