### 10.4 ASSESSMENT OF AEs AND SAEs

Seriousness, causality, severity and expectedness will be assessed as though the participant is taking active IMP. Cases that are considered serious and possibly related to IMP and unexpected (i.e. SUSARs) will be unblinded.

The Investigator is responsible for assessing each AE.

The Chief Investigator (CI) may not downgrade an event that has been assessed by an Investigator as an SAE or SUSAR, but can upgrade an AE to an SAE, SAR or SUSAR if appropriate.

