#### 10.4.2 Assessment of Causality

The Investigator will make an assessment of whether the AE/SAE is likely to be related to the IMP according to the definitions below.

All AEs/SAEs judged as having a reasonable suspected causal relationship (ie possibly related) to the IMP will be considered as related to the IMP (ARs/SARs).

Where non Investigational Medicinal Products (NIMPs) e.g. rescue/escape drugs are given: if the AE is considered to be related to an interaction between the IMP and the NIMP, or where the AE might be linked to either the IMP or the NIMP but cannot be clearly attributed to either one of these, the event will be considered as an AR/SAR.

Unrelated: where an event is not considered to be related to the IMP.

Possibly Related: Possibly Related: The nature of the event, the underlying medical condition, concomitant medication or temporal relationship make it possible that the AE has a causal relationship to the study drug.

Alternative causes such as natural history of the underlying disease, other risk factors and the temporal relationship of the event to the treatment should be considered and investigated. The blind should not be broken for the purpose of making this assessment.

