#### 10.4.3 Assessment of Severity

The Investigator will make an assessment of severity for each AE/SAE and record this on the CRF or AE form according to one of the following categories:

Mild: an event that is easily tolerated by the participant, causing minimal discomfort and not interfering with every day activities.

Moderate: an event that is sufficiently discomforting to interfere with normal everyday activities.

Severe: an event that prevents normal everyday activities.

Note: the term 'severe', used to describe the intensity, should not be confused with 'serious' which is a regulatory definition based on participant/event outcome or action criteria. For example, a headache may be severe but not serious, while a minor stroke is serious but may not be severe.

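### Visit 4 lists unblinding before the treatment diary is collected, so adverse events first found in the diary may be graded with the allocation known

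*Protocol*

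**What the plan says.** Section 7.2 lists four items for the 6-month visit, in this order: questionnaire, unblinding, "Collection of treatment diary", and collection of unused study medication. Section 3 states who learns the allocation and when: "Participants and the health care team will be unblinded at the end of their treatment".

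The diary is issued at randomisation (section 6.5) and kept daily. Under section 7.2 it holds doses taken, reasons for dose changes, concomitant treatment, adverse events and a weekly average pain score. Section 10 confirms its safety role: "Participants will collect information about adverse events in their treatment diaries".

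Grading belongs to the Investigator. Section 10.4 says "The Investigator is responsible for assessing each AE", and section 10.4.3 says "The Investigator will make an assessment of severity for each AE/SAE and record this on the CRF or AE form". Two provisions protect that grading. Section 10.4 sets a convention, "Seriousness, causality, severity and expectedness will be assessed as though the participant is taking active IMP", and section 10.4.2 says of causality "The blind should not be broken for the purpose of making this assessment".

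**The concern.** Causality and severity of non-serious events are matters of judgement. Severity in section 10.4.3 turns on discomfort and interference with everyday activities. Dizziness or somnolence in a woman known to be taking gabapentin is more readily called related, or graded higher, than the same complaint in a woman known to be taking placebo. A trial that is blinded throughout treatment should not lose that protection at the moment the main participant-held record of adverse events is handed over.

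The diary is also a data source in its own right. Section 9.2(ii) draws self-reported compliance from it, and one of the two primary endpoints (section 2.2.1) includes taking all medication. Section 8 plans an anonymous questionnaire, after the diaries are submitted, on how well they were kept, so the investigators already expect imperfect completion. If a woman still holds the diary when she learns her arm, late or altered entries made with that knowledge are possible.

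**Working it through.** No formula applies, and the protocol gives no figure to reproduce. The check is to set the sections side by side.

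1. **Is the Visit 4 list a sequence?** It is not declared to be one. Two features suggest it. Visit 1 runs in time order, from consent through screening and eligibility to randomisation and issue of the diary. The 6-month questionnaire asks each woman which treatment she believed she was receiving (section 8), so it has to come before unblinding, as it does in the list.

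2. **Is the diary collected earlier anywhere?** No. In section 7.2, Visits 2 and 3 list an interview or questionnaire and dispensing, with fMRI for the Edinburgh subset at Visit 3. Visit 4 is the only visit that lists diary collection.

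3. **Does any section require diary events to be graded before disclosure?** No. Section 10.3 requires the Investigator to review the documentation and record each event with severity and causality, but gives no timing relative to unblinding. Sections 3, 10.2 and 10.4 give none either.

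4. **Could an event come to light first in the diary?** Yes. Telephone interviews are listed for weeks 1 to 5, and sections 6.3 and 10 continue weekly contact until the optimal dose is reached. After that, the listed contacts are the visits at week 6, 3 months and 6 months, plus focus groups or interviews for a subset between 3 and 6 months. Taking 3 months as about 13 weeks and 6 months as about 26, 13/26 = 50% of treatment lies between the last two visits. Once the dose is settled, no routine safety contact with all participants is listed in that half. A mild event that is written down but not telephoned in could stay in the diary until Visit 4.

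5. **How many are affected?** This cannot be derived. At 80% to 90% retention, 0.8 × 60 = 48 to 0.9 × 60 = 54 women would reach Visit 4. That counts attenders. The women who matter are those with an event recorded only in the diary, and the protocol gives no basis for estimating their number.

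**The case against.** A reader might infer that the protocol orders the Investigator to grade diary events unblinded, and that this contradicts section 10.4.2. The text does not support that.

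- The Visit 4 list is unnumbered and carries no words of order. The same section places the 3 to 6 month focus groups after the 6-month items, so it is not strictly chronological. It also refers to an appendix for further detail, and the flowcharts are not reproduced in the text available.
- Section 10.4.2 forbids breaking the blind for the purpose of judging causality. Planned end-of-treatment unblinding has another purpose, so there is no literal contradiction. The provision shows only that blinded judgement was intended.
- Section 3 names the health care team, not the Investigator.
- The active-drug convention in section 10.4 is a stated control, and it addresses the dizziness example directly.
- Other routes operate while the blind holds. Section 10 says "Participants will be instructed to contact their Investigator at any time after consenting to join the trial if any symptoms develop", and section 10.2 requires open-ended questioning, which could take place at Visit 4 before disclosure. Serious events are reported to the sponsor's office immediately or within 24 hours (section 10.5).
- Section 9.2 plans no between-arm comparison of adverse event causality or severity.

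All of this stands, and it narrows the point to non-serious events first found in the diary. It does not close the gap. The convention asks an assessor to set aside an allocation that may already be known, which limits bias without restoring the blind. The other routes reduce the number of diary-only events without eliminating them. That a woman might alter her diary after disclosure is a possibility only, since entries are meant to be daily and collection is at the same visit.

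**Conclusion.** The protocol permits, and its listed order invites, unblinded grading of non-serious adverse events that first come to light in the diary. It also leaves the dose and pain record with the woman when she learns her arm. This is a risk left open, not a prescribed procedure. It rests on two assumptions: that sites follow Visit 4 in the order listed, and that whoever grades the events is told the allocation as part of, or along with, the health care team. Neither the number of events nor the size of any rating bias can be derived from the document. For a 60-woman feasibility pilot with no planned between-arm adverse event comparison the effect is modest. The change is still worth making, because it costs almost nothing and because the pilot's methods are meant to inform the definitive trial.

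**What to change.** Reorder Visit 4 in section 7.2 as: questionnaire; collection of diary and unused medication; recording of diary adverse events in the CRF with severity and causality; then unblinding. Add one sentence to sections 3 and 10.3 stating that these assessments are completed for each participant before her planned end-of-treatment disclosure. State that emergency unblinding and unblinding of SUSARs are unaffected. Check that the flowcharts show the same order.

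The cost is one reordered list and one added sentence in each of the two sections. The downside is a slightly longer final visit, or slightly later disclosure to the participant and her health care team.
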